**Fig. 1 Fig1:**
[figure not shown]
Flow of participants through the study

### Study settings

The study is conducted in the outpatient unit of the Physiotherapy Department at Ahmadu Bello University Teaching Hospital (ABUTH), Zaria, Kaduna State, Nigeria.

### Eligibility criteria

The following are the inclusion criteria for patient selection:Both male and female diabetic patients (both type 1 and 2) aged 20 to 65 years old [8].Patients with shoulder pain within the last 3 months (painful or first stage).Patients with decreased active glenohumeral ROM of at least 20° or more in at least three movements: flexion < 144°, abduction < 120° and external rotation < 72° [47].Patients having bilateral or unilateral shoulder symptoms.

The following are the exclusion criteria for patient selection:Patients with a history of trauma to the shoulder.Neurological involvement such as stroke, brachial plexus injury, Parkinson's disease, and cervical spine injury with or without radiculopathy.History of surgery to the shoulder, malignancy, or tumour of the shoulder.Shoulder arthritis, rotator cuff tear, or other shoulder ligamentous injury.

### Informed consent

The physiotherapist responsible for eligibility assessment will obtain written informed consent from the participants after explaining the study procedure. During the study period, all potential participants will have the opportunity to withdraw at any time point during the study period.

### Additional consent provisions for collection and use of participant data and biological specimens

Not applicable. Data and biological specimens will not be collected for ancillary studies.

### Explanation for the choice of comparators

Therapeutic exercises including flexibility and strength training are commonly used by physiotherapists to manage frozen shoulder and, hence considered to be an established treatment or standard of care. Our trial is designed to compare two experimental interventions (LLLT and MET) with therapeutic exercises– here referred to as CTE as the control intervention. The active control group will help to mitigate the possibility that improvements seen in the experimental groups are due to a placebo effect.

### Intervention description

The control group will receive CTE only. In the LLLT group, participants will receive LLLT followed by CTE. Similarly, participants allocated to MET group will receive MET followed by the same CTE. All interventions will be administered three times per week for 8 weeks, equivalent to a total of 24 treatment sessions. The participants will be treated on alternate days to minimise group contamination. The primary researcher who has over 13 years of clinical experience in musculoskeletal physiotherapy will administer all the interventions. Another licensed physiotherapist with 5 years of clinical experience will assist in administering the CTE. For patients presenting with bilateral affectation, both shoulders will be treated.

### Conventional therapeutic exercises (CTE)

Eight CTE aiming to improve shoulder ROM (i.e. flexion, abduction adduction, and external and internal rotation) and strength will be administered. Each exercise will be repeated 5–10 times per session. Progression of exercise will be based on the patient's pain thresholds or tolerance. The exercises include:Pendulum exercise: The participant’s position will be standing or prone lying. The patient leans forward in standing by supporting the unaffected shoulder on a plinth. The affected shoulder is hung down parallel with the trunk and then swings forward and backward side to side or around in circles.Arm overhead exercise: The participant lies supine and supports the affected arm with the unaffected hand. The participant then lifts the affected arm overhead.Finger wall ladder: The participant slowly walks his finger up the wall and slowly lowers the arm.Twisting arm outwards: The participant lies supine with the knees bent, and then places the hand behind the neck or head and lets elbows fall outwards.Overhead pulley: The participant sits on a chair, and grasps one handle with the affected side overhead with the palm facing inward. The unaffected hand grasps the other handle with the elbow flexed, and gently stretches the affected shoulder overhead by extending the elbow.Cross-body reach exercises: The participant stands and takes the affected hand across towards the opposite shoulder, and then stretches gently by pulling the affected arm at the elbow and holds for 10–15 s.Hand behind-back exercise: The participant stands with arms by side, grasps the affected wrist, stretches the hand towards the unaffected shoulder, and slides the arm up the back. The exercise can be progressed to the use of a towel.Outward rotation exercise: The participant stands, holds a rubber band or TheraBand with the elbow at 90°, and then rotates the affected arm outward while holding for 5 s.

### Low-level laser therapy (LLLT)

Laser treatment will be applied using a Class 3B Laser therapy unit (I-TECH LA 500), with a wavelength of 810 nm, continuous output power of 60 Mw, and spot size/area of 0.5 cm^2^, similar to the protocol described by Stergioulas [48]. Painful areas of the shoulder such as the subacromial space, bicep anchor, axillary pouch, anterior shoulder capsule, and posterior shoulder capsule will be irradiated with a power density of 5.4 j/cm^2^ and duty cycle of 50%. The application time will be 30 s per area. Prior to application, the area to be treated will be cleaned with methylated spirit to minimize reflection from skin and probe [48]. Rotation interval and probe will be perpendicular to the circumscribed area thereby preventing energy loss due to divergence. Both the therapist and participant will wear protective eye goggles during the treatment as a safety measure.

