Among the several electrotherapy modalities employed in physiotherapy, low-level laser therapy (LLLT) emerges as a promising modality for the treatment of frozen shoulder owing to its analgesic, anti‐inflammatory and biostimulating effects [34]. A class IIIa LLLT with a power output of < 5mW or a class IIIb LLLT with a power output of < 500 mW is often applied to achieve optimal therapeutic effect [35]. However, LLLT is typically used in combination with other therapies such as exercise rather than in isolation. While moderate evidence indicates that LLLT offers added short-term pain relief benefits when combined with exercise, evidence for additional benefits on shoulder function and ROM is limited [36].

One hands-on technique commonly used by physiotherapists to manage MSKD such as frozen shoulder is the muscle energy technique (MET) [37, 38]. It is a class of gentle soft tissue manipulation applied to lengthen shortened, contracted, or spastic muscles, strengthen weak muscles, decrease edema and passive congestion, correct faulty joint positions, as well as mobilise restricted or hypomobile joints [39, 40]. As frozen shoulder often involves inflammation, reduced ROM and pain, the use of MET to address  these symptoms is crucial [41]. While MET has shown effectiveness in improving pain, disability, and ROM in various MSKDs, its efficacy in frozen shoulder specifically requires further evaluation [42]. Morever, existing trials on MET for frozen shoulder [43–46] have yielded conflicting results and lack methodological robustness.

Frozen shoulder constitutes a major burden in patients with diabetes, yet the most optimal treatment remains obscure. Although both LLLT and MET are used to manage frozen shoulder, the superiority of one intervention over the other has not been explored. Moreover, no study has evaluated the effect of either intervention on inflammatory biomarkers or psychological variables. Given that both LLLT and MET could alleviate pain and enhance function, which may result in improved psychological well-being, it is probable that such interventions could positively influence depression, anxiety as well as QoL. As there has been no investigation into the effectiveness of LLLT and MET and their comparison through a well-conducted randomised controlled trial (RCT) among diabetic patients with frozen shoulder, this study will be conducted to assess the comparative effectiveness of LLLT versus MET among diabetic patients with frozen shoulder.

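### The stated laser settings do not give the stated energy density: 60 mW for 30 s on 0.5 cm² is 3.6 J/cm² (or 1.8 at a 50% duty cycle), not 5.4

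*Protocol article*

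**What the plan says.** All the laser settings stand in one paragraph of the protocol article, under Low-level laser therapy (LLLT). The device is a Class 3B unit with "continuous output power of 60 Mw, and spot size/area of 0.5 cm^2". Painful areas of the shoulder, with five sites named as examples, are to be "irradiated with a power density of 5.4 j/cm^2^ and duty cycle of 50" per cent. On duration: "The application time will be 30 s per area". The settings are described as resembling those of a cited earlier protocol. The paragraph does not derive the 5.4, give a pulse frequency, distinguish peak from mean power, or mention repeat passes over an area.

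Under Intervention description, the LLLT group receives the laser and then the same conventional therapeutic exercises (CTE) that the control group receives alone. The schedule is three sessions a week for 8 weeks, 24 in all.

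**The concern.** Power, exposure time, spot area and energy density are tied by one identity, so any three fix the fourth. The paragraph states all four, and the fourth does not follow from the other three. The duty cycle is a fifth figure bearing on the same identity, and the text does not say how it combines with an output described as continuous.

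This is more than an editorial matter because of what the laser does in the design. CTE is common to all arms, so the laser exposure is the whole difference between the LLLT arm and control. If that exposure is known only to within a factor of 1.5 to 3, neither a positive nor a null LLLT result can be attached to a defined treatment, and another group could not repeat it. The article says its findings may guide practice, which requires that a reader can tell what was given.

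**Working it through.** **Inputs** (all from the LLLT section unless noted)

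- Power P: "continuous output power of 60 Mw", read as 60 mW = 0.060 W. The milliwatt reading is an assumption. It is supported by the Background, which describes "a class IIIb LLLT with a power output of < 500 mW".
- Area A: 0.5 cm².
- Time t: 30 s per area.
- Duty cycle d: 50%, or d = 1 if the beam is continuous.
- Stated energy density: 5.4 J/cm².

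**Formula.** Energy per area (J) = P × d × t. Energy density (J/cm²) = P × d × t / A.

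**Attempt to reproduce 5.4**

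| Reading | Energy per area | Energy density | Stated 5.4 relative to it |
|---|---|---|---|
| Continuous, 60 mW | 0.060 × 30 = 1.8 J | 1.8 / 0.5 = 3.6 J/cm² | 5.4 / 3.6 = 1.5 |
| Gated at 50%, 60 mW is peak | 0.060 × 0.5 × 30 = 0.9 J | 0.9 / 0.5 = 1.8 J/cm² | 5.4 / 1.8 = 3.0 |
| Gated at 50%, 60 mW is mean (peak 120 mW) | 0.120 × 0.5 × 30 = 1.8 J | 1.8 / 0.5 = 3.6 J/cm² | 1.5 |

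The stated figure is not reproduced.

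**Other readings tried**

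- *Rounding.* Let all three inputs vary generously (55–65 mW, 29.5–30.5 s, 0.45–0.55 cm²). Continuous output then spans 0.055 × 29.5 / 0.55 = 2.95 to 0.065 × 30.5 / 0.45 = 4.41 J/cm². Gating at 50% halves these. Neither range reaches 5.4.
- *0.5 as a length in cm instead of an area.* As a diameter (0.1963 cm²): 9.17 continuous, 4.58 gated. As a radius (0.7854 cm²): 2.29 and 1.15. As the side of a square (0.25 cm²): 7.2 and 3.6. None is 5.4.
- *5.4 as a true power density.* That would be 60 mW / 0.5 cm² = 120 mW/cm², or 60 mW/cm² averaged over a 50% duty cycle. The number does not fit, and the printed unit is one of energy density in any case.
- *5.4 as a total.* Three passes at 1.8 J/cm² (gated, 60 mW peak) sum to 5.4 J/cm². In plain joules, 3 × 1.8 J (continuous) or 6 × 0.9 J (gated) also give 5.4. The text describes no three- or six-fold repetition, and the five example sites do not match: 5 × 3.6 = 18 and 5 × 1.8 = 9.

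**Emission mode.** Side by side, the paragraph has "continuous output power of 60 Mw" and, in the next sentence, "duty cycle of 50" per cent. If the beam is continuous, the duty cycle has no function. If it is gated, the dose depends on whether 60 mW is peak or mean, which is not stated. Neither choice yields 5.4.

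**The case against.** Several points can fairly be made on the other side.

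- *Continuous may be a rating.* The phrase occurs in the list of device characteristics, and the duty cycle comes later, where application is described. The beam could be rated at 60 mW and then gated. This stands: it makes the mode an ambiguity of wording and not a physical impossibility. It does not help the dose, which becomes 1.8 J/cm² if the 60 mW rating is the peak.
- *Something may be unstated.* Three passes would reconcile 5.4 with the gated reading. This too stands as a possibility, so one cannot insist that a printed value must be wrong. But the text gives no hint of repeats.
- *The factor of 3 is not certain.* It applies only if 60 mW is peak power. If it is the mean, or the beam is continuous, the gap is 1.5-fold.
- *The unit slip is trivial.* Mw is plainly a misprint for mW and carries no weight of its own. The power-density label is a real but minor error.
- *The cited protocol may settle it.* The article claims only resemblance to that protocol, so the source cannot decide which of the conflicting values applies here.

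A reader might also infer that different therapists, working from different lines of the paragraph, would deliver different doses. The document does not support this. Under Intervention description the primary researcher gives all interventions, the second physiotherapist assists only with CTE, and the trial has one centre and one named device. A reader might go further and infer that the comparison of arms is invalid. That does not follow either: whichever single setting was used, LLLT plus CTE against CTE remains a randomised comparison for that setting.

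**Conclusion.** The point holds as an internal contradiction in how one experimental arm is defined. The stated power, time and area give 3.6 J/cm², or 1.8 J/cm² if 60 mW is peak power at a 50% duty cycle. The stated 5.4 J/cm² is 1.5 or 3 times that, and no per-area reading tried recovers it. At least one value is wrong, or an element of the procedure is missing from the description. The emission mode and the meaning of 60 mW are undefined, and the energy density is mislabelled.

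The conclusion rests on reading Mw as mW and on one 30 s exposure per area per session, as written. The harm lies in interpretation and reproducibility of the LLLT result. Randomisation, blinding, outcomes, sample size and analysis are untouched. It still needs correcting before results are reported, because without it the exposure in that arm is unknown to the reader.

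**What to change.** Reconcile these items against the settings actually used on the device, so that power × duty cycle × time / area equals the stated energy density:

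- power, marked as peak or mean;
- emission mode and duty cycle;
- spot area;
- exposure time per area, with the number of passes if more than one;
- energy density.

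Then correct the power unit, relabel the J/cm² figure as an energy density, and state in the results paper the energy density actually delivered. Which values stand is for the clinical team to decide; nothing here favours one.

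The cost is small: a check of the device settings and treatment records, and a clarification of the protocol. According to Trial status, recruitment opened on 2 February 2023 and was expected to end by May 2024, and the article appeared on 30 April 2024. Much of the treatment had therefore probably been given by then (an inference from the dates), and the task is mainly to describe correctly what was done. If the check shows that settings changed during the trial, that should be reported too.

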### Muscle energy technique (MET)

This will be administered for restriction in shoulder flexion, abduction, and external rotation. The treatment protocol procedure described in this study is identical to that described in the literature [36].MET for shoulder flexion restriction: The participant will be in a side-lying position with the affected shoulder uppermost and the therapist will stand at chest level of the participant with one hand holding the patient's forearm and the other hand stabilising the participant's clavicle and scapula. While maintaining the participant's uppermost shoulder into flexion passively, the patient will be instructed to pull the elbow towards the feet by utilising approximately 20% maximal effort. The therapist will firmly resist this effort for 7–10 s and then move the shoulder arm into further flexion to the next restriction barrier. The treatment protocol will be repeated 3 times per session. The targeted muscles are the deltoid, pectoralis major, biceps brachii, subscapularis, and latissimus dorsi.MET for shoulder abduction restriction: The participant will be in a supine and the therapist will stand at the side with one hand holding the participant's flexed elbow and the other hand stabilising the patient's clavicle and scapula. The therapist will then horizontally adduct the participant's shoulder to the initial point of pain or barrier and instruct the participants to pull the arm while utilising approximately 20% maximal effort. The therapist will firmly resist this effort for 7–10 s and instruct the participant to relax, and while exhaling, the therapist, using his contact on the elbow, moves the participant’s shoulder further into abduction. The treatment protocol will be repeated 3 times per session. The targeted muscles are the deltoid, supraspinatus, infraspinatus, teres minor, and subscapularis.MET for shoulder external rotation restriction: The participant will be in a supine position with the arm abducted to 90°, the elbow flexed to 90°, the forearm in internal rotation, and the palm facing upward. If the participant cannot abduct or flex to 90°, the available range will be the starting point and gradually increase as the participant improves. The therapist stands at the side with one hand holding the participant's forearm and the other hand stabilising the participant's clavicle and scapula. While the participant's entire arm is resting at the restriction barrier, with gravity as its counterweight, the participant will be instructed to raise the forearm slightly, against minimal resistance provided by the therapist, for 7–10 s. Following relaxation, gravity or slight assistance from the therapist takes the arm into greater external rotation, through the barrier, where it will be held for 30 s. The treatment protocol will be repeated 3 times per session. The targeted muscles are the infraspinatus, teres minor, and posterior deltoid.

### Criteria for discontinuing or modifying allocated interventions

No provisions for changing the trial arm allocation. However, the criteria for discontinuing the allocated interventions will be participant withdrawal of consent at any point of the study without providing reasons and participant experiencing worsening of condition related to other diabetic complications. Any data collected up to the point of withdrawal will be included in the study and intention-to-treat analyses will be conducted.

### Strategies to improve adherence to interventions

To ensure intervention adherence during the trial period, all participants will be well informed during the consent process about the importance of completing all treatment sessions and outcome measurements post 8-week intervention and at 3 months follow-up.

### Relevant concomitant care permitted or prohibited during trial

Relevant concomitant care and interventions will be permissible during the trial other than administration of other experimental treatments that might influence or bias the study outcomes.

### Provisions for post-trial care

We will document any adverse events (AEs) within the current study and ensure that appropriate care is provided to study participants if necessary.

### Outcomes

Two independent assessors (licensed physiotherapists) who will be trained by the primary researcher ([name]) before participating in the trial and blinded to group allocation will assess all outcome measures prior to randomisation. For patients with bilateral shoulder affectation, the more painful side will be chosen for outcome assessment.

### Baseline data collection

Sociodemographic characteristics (e.g. age, gender, marital status, education level, occupational level, height, weight, and body mass index) and clinical characteristics (e.g. duration of DM, type of DM, affected side, smoking status, alcohol status, presence of comorbidity, fasting glucose level and two-hour post-prandial blood glucose) will be obtained and recorded using a prepared study proforma. All participants will be given a specific ID for recognition.

### Primary outcome measure

The primary outcome measure is the shoulder function to be assessed using the Shoulder Pain and Disability Index (SPADI). It consists of 13 items divided into two subscales (5 items for shoulder pain and 8 items for shoulder disability). Each item is scored on a 0–10 numerical rating scale, where 0 denotes the best score and 10 denotes the worst score [49]. The scores of each subscale are added up and converted into a score out of 100, with higher scores indicating greater pain and disability [50]. The SPADI is a valid, reliable, and responsive measure of shoulder pain and disability [50–52]. Both the English [53] and Hausa (unpublished data) versions will be used in this study.

### Secondary outcome measures

The secondary outcome measures include pain intensity, shoulder ROM, depression, anxiety, QoL, and IL-6.Pain intensity: The participants’ shoulder pain intensity will be assessed using the Numerical Pain Rating Scale (NPRS). It is an 11-point Likert scale, with 0 representing “no pain” and 10 representing “worst imaginable pain". The participants will be asked to mark or cycle the best point that represents the greatest pain they experienced at the time of assessment. The NPRS is a valid, reliable, and responsive measure of pain intensity in patients with shoulder pain [54, 55]. Both the English [56] and Hausa [57] versions will be used in this study.Shoulder ROM: The participants’ painful shoulder range of flexion, abduction, and external rotation will be measured in a supine position using a 12-inch, 360-degree goniometer (G30, China) in line with standardised instructions [58, 59]. The universal goniometer was reported to have adequate reliability with intraclass correlation coefficients (ICC) of 0.91 to 0.99) in measuring shoulder ROM [60]. In the present study, the reliability of the shoulder ROM measurements will be checked by an external assessor.Interleukin-6: Venous blood samples of the participants will be obtained and processed at the Immunology Unit of Medical laboratory Department, ABUTH, Zaria. The participant's venous blood (from the median cubital vein or the cephalic vein) using plain bottles containing 50 µL of aprotinin will be collected by a well-trained laboratory technician and the plasma will be stored at − 80 °C until analysis. The serum level of IL-6 will be then processed by a medical laboratory scientist, using enzyme-linked immunosorbent assay (ELISA) method with high-sensitivity kits (Quantikine®HS, R&D Systems Minneapolis, U.S.).Anxiety and depression: Participants' levels of depression and anxiety will be assessed using the Hospital Anxiety and Depression Scale (HADS). It consists of 14 items divided into 2 subscales, with 7 items for anxiety and 7 items for depression. Each item is rated on a 4-point Likert scale (range 0–3). The total score is the sum of the 14 items, and for each subscale, the score is the sum of the respective 7 items ranging from 0–21. Scores of 0–7 indicate 'no case', 8–10 indicate 'possible case', and > 11 indicate a 'probable case of anxiety/depression' [61]. The HADS is a valid, reliable, and responsive measure of anxiety and depression in different patient populations as well as the general population [62]. Both the English [61] and Hausa (unpublished data) versions will be used in this study.Quality of life (QoL): Participants’ QoL will be assessed using the 36-item short-form health survey (SF-36). The questionnaire consists of 36 items that are clustered to yield 8 domains of health status: physical functioning (PF), role-physical (RP), bodily pain (BP), general health (GH), vitality (VT), social functioning (SF), role-emotional (RE), and mental health (MH). Two summary measures, namely the physical component summary (PCS-12) and mental component summary (MCS-12) scores can be obtained from the 8 domains. Each domain and summary scale is scored 0–100, with higher scores indicating higher levels of function and/or better health [63, 64]. The scoring of the SF-36 will be computed using standard published guidelines [65]. The SF-36 has shown good psychometric properties in patients with shoulder disorders [66]. Both the English [63] and Hausa (unpublished data) versions will be used in this study.
